## Abstract

**Background:**

A recent Dutch mono-centre randomised controlled trial has shown that occupational therapy improves daily functioning in dementia. The aim of this present study is to compare the effects of the Dutch community occupational therapy programme with a community occupational therapy consultation on daily functioning in older people with mild or moderate dementia and their primary caregivers in a German multi-centre context.

**Methods/Design:**

A multi-centre single blind randomised controlled trial design is being used in seven health care centres (neurological, psychiatric and for older people) in urban regions. Patients are 1:1 randomised to treatment or control group. Assessors are blind to group assignment and perform measurements on both groups at baseline, directly after intervention at 6 weeks and at 16, 26 and 52 weeks follow-up. A sample of 140 community dwelling older people (aged >65 years) with mild or moderate dementia and their primary caregivers is planned. The experimental intervention consists of an evidence-based community occupational therapy programme including 10 sessions occupational therapy at home. The control intervention consists of one community occupational therapy consultation based on information material of the Alzheimer Society. Providers of both interventions are occupational therapists experienced in treatment of cognitively impaired older people and trained in both programmes. 'Community' indicates that occupational therapy intervention occurs in the person's own home. The primary outcome is patients' daily functioning assessed with the performance scale of the Interview for Deterioration in Daily Living Activities in Dementia and video tapes of daily activities rated by external raters blind to group assignment using the Perceive, Recall, Plan and Perform System of Task Analysis. Secondary outcomes are patients' and caregivers' quality of life, mood and satisfaction with treatment; the caregiver's sense of competence, caregiver's diary (medication, resource utilisation, time of informal care); and the incidence of long-term institutionalisation. Process evaluation is performed by questionnaires and focus group discussion.

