### Outcomes

The primary endpoint is the comparison between the intervention group and control group in the change in daily functioning from baseline to follow-up as indicated by the Interview for Deterioration in Daily Living Activities in Dementia (IDDD) over three post intervention time points. The WHEDA measurement scheme with dependent variables and measurement instruments is provided in table 1. The primary and most secondary outcomes are oriented to patient and caregiver. Daily functioning, quality of life, mood and daily interaction are directly related to individual everyday life and represent the user's perspective in most self- and proxy-assessments used in the WHEDA study. It is of great importance to know how long a therapeutic approach may stabilise daily functioning after the intervention is finished. The cognitive decline in dementia is a strain on patients and caregivers. Its progress varies, but major and consistent changes are mostly not observable before a half year progress of disease. Consequently, the follow-up assessments are appointed at week 16 and 26 after baseline. In order to justify a potential implementation in practice, service providers as well as political and economical decision-makers within the health care system need trustworthy evidence about an innovative intervention. Hence feasibility, acceptance and costs of active and control treatment are additional outcomes of the WHEDA study.

**Table 1 T1:** WHEDA measurement scheme

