**Primary outcome**												
Patients' functioning in everyday life	IDDD, PRPP-Video rating		X	X		X		X				

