#### Primary outcome measures

• The Interview of Deterioration in Daily Living Activities in Dementia (IDDD [39]) consists of two scales recording the caregivers' rating of patients' initiative and performance of daily living activities. The *Initiative Scale *measures the initiative for (1) washing oneself, (2) making tea or coffee, (3) dressing, (4) combing one's hair and brushing one's teeth, (5) shopping, (6) using the phone, (7) preparing a meal, (8) cleaning the house or doing minor repair work and (9) handling finances. The *Performance Scale *records the need of assistance in the performance of the same nine activities plus eating and using the toilet. Both domains of the IDDD are constructed as five-point-Likert-scales with the ratings never = 4, seldom = 3, sometimes = 2, often = 1, always = 0 in the *Initiative Scale *and values vice versa in the *Performance Scale*. Scores of the *Initiative Scale *range from 0 to 36 (higher scores indicate less initiative). The *Performance Score *ranges from 0 to 44 (higher scores indicate higher need for assistance). In a Spanish sample of 451 persons, the IDDD demonstrated great internal consistency (Cronbach's alpha = .99), reproducibility (intraclass correlation coefficient ICC = .94) and significant differences between groups of patients with mild cognitive impairment and patients with dementia [40]. In a Dutch sample of 25 primary and secondary caregiver pairs, the IDDD interrater reliability was high (ICC: .85 for the *Initiative Scale *and .74 for the *Performance Scale*, [39]). Within the Dutch original study the *Performance Scale *demonstrated a very high responsiveness by indicating clinically relevant improvement in 78% of cases in the intervention group and 12% of cases in the control group 6 weeks after baseline and 82% and 10% respective after 12 weeks [26].

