• With the Perceive, Recall, Plan and Perform System of Task Analysis (PRPP) occupational therapists evaluate a usual daily activity as performed by the patient as well as the impact of the cognitive performance component on this performance [41]. In the first of two assessment stages, the rater defines single steps of the performed activity to be analysed and identifies any activity step in which errors of accuracy, omission, repetition or timing occur. The number of activity steps rated as incorrectly performed is divided by the total number of activity steps, resulting in an independence-score indicated in percent (100% = all steps are error-free). In the second stage, the therapist rates 34 items of observable behaviour representing the patients' use of information processing strategies while performing the activity. On the three-point-Likert-scale the value 1 indicates incomplete or non-timely or jeopardising task performance or the need of significant assistance. Value 2 indicates a complete and non-jeopardising task performance but with problems in timing and possible need of assistance. Value 3 indicates a complete, timely and non-jeopardising task performance without any need of assistance. The 34 unweighted items are summed up by four main scales Perceive, Recall, Plan and Perform each with three subscales and a PRPP global processing score ranging from 35 to 103 (higher scores denotes better performance). The PRPP-System was systematically developed over the last 12 years including the following steps and results [41]:

◦ Content validity was shown in a comparative analysis of the same activities of daily living in a sample of 25 healthy adults and a sample of 20 persons with brain injury. Variations of individual performance but no errors occurred within the healthy sample whereas clearly observable errors within the sample with brain injury could be catalogued in the four main categories accuracy, omission, repetition or timing. Interrater agreement of six raters was high (>90%) for both samples.

◦ A microanalysis of more than 4000 errors occurring in the performance of dressing, eating and grooming of 45 patients with brain injury revealed four broad errors types in cognitive processes of perceiving, recalling, planning and performing. Error analyses in subsequent investigations of other samples led to a stable pattern of 34 items which describe observable behaviour.

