### Statistical methods

Data are entered via special MS Access entry masks automatically controlling for data plausibility. In addition, sections of entered data are checked for typing errors by hand, in order to ensure an error rate lower than 0.2%. Baseline measures and demographics of participants significantly differing at baseline in intervention and control group and control measures are used as co-variates in an analysis of variance with repeated measures with two groups and four measurement time points. If the diagnosis of extent and type of missing data reveal that the precondition is given, the Full Information Maximum Likelihood (FIML) method will be applied for data replacement [73]. The primary intention-to-treat analysis, including all participants with valid data (whether they did or did not receive the intervention), will be compared with a per protocol analysis excluding all participants with documented deviations from the protocol (ie. not receiving the entire intervention or receiving an incomplete follow-up). The comparison of these groups will be adjusted for baseline imbalance and process variations. Variations in the adherence to protocol; to the treatment manual and to therapeutic recommendations; variations in medication and progress of cognitive decline as well as variations in the quality of supporting or hindering structures and processes at the study sites are considered as possible mediators. All statistical tests will be two-sided on an alpha level of .05.

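### The protocol contradicts itself on the primary endpoint: IDDD and PRPP together in some places, IDDD alone with its scale unnamed in another, with a sample size for one IDDD test at .05

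*Protocol article*

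**What the plan says.** The protocol article describes the primary outcome in four places, and they do not agree.

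- **Abstract, Methods/Design:** "The primary outcome is patients' daily functioning assessed with the performance scale of the Interview for Deterioration in Daily Living Activities in Dementia". The same sentence adds a second source, so that the pair reads: "Interview for Deterioration in Daily Living Activities in Dementia and video tapes of daily activities rated by external raters blind to group assignment", with the PRPP as the rating system. This gives two measures. The IDDD scale is named; the PRPP score is not.
- **Outcomes:** the primary endpoint is the group comparison of change in daily functioning "as indicated by the Interview for Deterioration in Daily Living Activities in Dementia (IDDD) over three post intervention time points". This gives one instrument, with no scale named and no PRPP.
- **Table 1, Primary outcome row:** "IDDD, PRPP-Video rating". This gives two instruments, with no scale or score named.
- **Primary outcome measures:** the IDDD "consists of two scales recording the caregivers' rating of patients' initiative and performance of daily living activities", followed by the PRPP with an independence score, four main scales and a global score.

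The Sample size section takes the earlier Dutch effect from the IDDD performance scale. Item 4 of the Discussion says that power rests on the IDDD because no PRPP pilot data existed. Statistical methods sets the level: "All statistical tests will be two-sided on an alpha level of .05".

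On PRPP scoring, Primary outcome measures says: "The number of activity steps rated as incorrectly performed is divided by the total number of activity steps", with 100% meaning that no step contained an error. It also gives a "PRPP global processing score ranging from 35 to 103" for 34 items, each scored 1 to 3.

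**The concern.** The primary endpoint decides whether the trial is called positive, so the document should give one answer. Here a reader can find support for the IDDD alone or for the IDDD and PRPP jointly.

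The choice matters because the two instruments carry different risks of bias. The IDDD is the caregiver's rating. The Randomisation section says caregivers cannot be masked, and in the COTP arm the same caregivers are trained as part of the intervention. The same section describes the video rating as the procedure that secures full blinding. A positive caregiver rating beside a null blinded rating, or the reverse, is a realistic result. The text does not say which of the two would be the trial's answer.

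The PRPP section adds a smaller problem. Its scoring rule contradicts its own label, and its stated range does not match its items.

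**Working it through.** **1. What the sample size covers.** Inputs from Sample size: two groups, four time points (m = 4), f = .10, correlation .7, two-sided alpha .05, power .80, N = 84. I used the group-by-time interaction in a repeated-measures analysis of variance, assuming sphericity.

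- Noncentrality = N × m × f² / (1 − correlation) = 84 × 4 × .01 / .3 = 11.2
- Degrees of freedom: 3 and 3 × (84 − 2) = 246
- Power at N = 84: 0.805. Power at N = 82: 0.794.

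The stated 84 is reproduced for a single test at .05. A between-group main-effect test with the same inputs would need 612, so the interaction test is evidently the one used. Nothing in the figure allows for a second primary test.

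**2. False-positive chance under each reading.** The level per test is .05 (Statistical methods). The document gives no correlation between IDDD and PRPP, so 0 to .9 is an assumed range. The independent case is 1 − .95² = .0975. The correlated cases come from simulated two-sided normal tests; 3-degree-of-freedom interaction tests differ by less than 0.2 percentage points.

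| Reading | Chance of a false-positive primary result |
|---|---|
| One named IDDD scale is the sole primary | 5% |
| Both IDDD and PRPP must be significant | at most 5% |
| Either may win, independent | 9.75% (1.95 times 5%) |
| Either may win, correlation .3 | 9.5% |
| Either may win, correlation .5 | 9.1% |
| Either may win, correlation .7 | 8.4% |
| Either may win, correlation .9 | 7.0% |

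Without any assumption on correlation, the upper bound for two tests is .05 + .05 = 10%.

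**3. What the two-measure readings cost in power.** These figures assume that f = .10 and the correlation of .7 between time points also hold for the PRPP, which the document does not claim.

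- *Either may win, .025 each:* the combined error is 1 − .975² = .0494 if independent. Power per test at N = 84 falls to 0.718, and 80% needs N = 100. With all 140 recruited persons analysed it would be 0.935.
- *Both required at .05:* if the tests were independent, power at N = 84 would be 0.805² ≈ 0.65. Positive correlation would raise it.

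**4. PRPP scoring.**

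- Independence score: with no errors, incorrect/total = 0/total = 0%, but the text assigns 100% to that case.
- Global score: minimum 34 × 1 = 34 and maximum 34 × 3 = 102, against the stated 35 and 103. The width is the same: 102 − 34 = 68 and 103 − 35 = 68.

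**The case against.** The strongest reply is that the text already leans one way. Outcomes is the only place that spells out a primary endpoint with a comparison and time points, and it uses the IDDD. Power was based on the IDDD, and 84 fits one test. The abstract names the performance scale, and Sample size cites that scale for the earlier effect. On this view there is one outcome domain, two instruments and one powered endpoint, labelled inconsistently. This is a good argument for how to resolve the conflict. It does not remove the conflict, because three other places call the PRPP primary.

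A second reply is that an article condenses the full protocol, and that a success rule or alpha allocation may stand in a document not shown. That is accepted: the absence of such a rule is not the finding. The finding is that the published definitions disagree.

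A reader might infer that the plan at least doubles its error rate, or that four scores (two IDDD, two PRPP) compete as primaries, which would give 1 − .95⁴ = 18.5% if independent. The documents do not support either inference. They state .05 per test and no overall rate, and never say that one positive measure is enough. For two measures 9.75% is the independent value, and positive correlation lowers it. No section designates the Initiative scale as an endpoint; it is described as part of the instrument.

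Nor do the PRPP slips show that results would be reversed. The note on 100% makes the intended direction clear, and a constant shift of one point in the range changes no group comparison.

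**Conclusion.** The contradiction stands and should be settled before unblinding, because it determines what counts as success. The size is conditional. If either measure could be claimed, or the choice were made after seeing the data, the false-positive chance would be up to about 10%: 9.75% under independence, about 7% to 9.5% at assumed correlations of .9 to .3. If both measures are required, or one IDDD scale governs, it does not exceed 5%. That the sample size fits a single IDDD test at .05 rests on a reproduced figure, not an assumption. The two PRPP scoring errors are confirmed by arithmetic and are minor.

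**What to change.** Before unblinding, name the IDDD Performance scale as the single primary endpoint at .05. This fits the abstract's choice of scale, the Outcomes definition and the basis of the power calculation, so 84 and .05 stay as they are. Make the PRPP global score a key secondary. Report it whatever the IDDD shows, as the blinded check, and make a confirmatory claim on it only after a significant IDDD result. Align the abstract, Table 1, Outcomes and Primary outcome measures.

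If the sponsor prefers to keep the PRPP co-primary, state whether either or both must be significant, name the PRPP score, set alpha to match and restate power. Step 3 of the working shows the scale of that cost.

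In the PRPP description, define the independence score as 100% × (total steps − incorrect steps) / total steps, and give the global range as 34 to 102.

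The preferred route costs wording only and needs no new data. Its real price is that the PRPP, the fully blinded measure, loses co-primary status, which is why its result should always be shown beside the IDDD.

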**Discussion:**

The transfer from the Dutch mono-centre design to the pragmatic multi-site trial in a German context implicates several changes in design issues including differences in recruitment time, training of interventionists and active control group treatment.

The study is registered under DRKS00000053 at the German register of clinical trials, which is connected to the International Clinical Trials Registry Platform.

## Background

Dementia is a progressive, irreversible neurodegenerative disorder. The main symptoms are decline of memory and other cognitive functions associated with deterioration in daily functioning [1]. Several types of dementia are differentiated by aetiology including 72% Alzheimer, 16% vascular and 11% other types [2]. In the year 2000, there were 7.1 million people with dementia and 493 million persons of working-age [3] within Europe. Age is associated with increasing prevalence [4] with rates estimated at 6% in people aged over 65 and 30% in the over 80s [5]. Incidence rates range from 1.4% [6] to 3.2% [7]. Wancata and colleagues [3] predict the number of people with dementia in Europe to be 16 million or above in the year 2050. Bickel [8] estimates these numbers for Germany at 1.2 million in 2010, 1.7 million in 2020 and 2.3 million in 2050. In Germany, more than two thirds of people with dementia are women. 50% of community dwelling people with need of nursing care suffer from dementia. The disease constitutes the main cause of admission to long-term nursing homes with 60% of nursing home residents being affected by dementia. However, in Germany the majority of people with dementia (60%) live in the community and receive care by family members [9].

Direct costs of dementia in the year 2003 were estimated at 156 billion USD worldwide and 60.5 billion USD in the EU-25 region [10]. Direct costs in Germany amount to 5.6 billion Euros in the year 2002, including the major part of 3.6 billion Euros for dementia care in nursing homes [11]. Considering direct and indirect costs in Germany, Hallauer et al. [12] calculated dementia costs of 43,767 Euros per year and per patient, divided into 2.5% medical costs (medication, consultation, hospital stays), 29.6% nursing care costs and 67.9% costs borne by the patients' families. International studies demonstrate similar results and confirm the fact that family caregivers bear the main burden of dementia [13,14].

Deficits in daily functioning are used as threshold criteria in standardized diagnostic procedure [15,16]. Within the progress of disablement, cognitive decline leads to limitations in activities of daily living, which often affect the quality of life of patient and caregiver [17]. The new International Classification of Functioning, Disability and Health [18] is based on the bio-psycho-social model of health and consequently assumes that the negative impact of cognitive deficits on activities can be diminished by improving facilitation in the patients' physical and social environment. The task performance of people with dementia can be improved by reducing distraction and arranging clear structures in the physical environment [19]. Research on caregiver interventions provides evidence that those educational and psychosocial approaches targeting at the optimisation of the social environment delay nursing home placement [20-22]. Tailoring the activity to patients' capability may enhance activity engagement and reduce challenging behaviour [23].

A Dutch intervention programme in dementia care systematically integrated environmental adaptations, support of caregivers as well as selecting and tailoring everyday activities with regard to patients' occupational preference and cognitive abilities [24]. This programme demonstrated positive impacts on patients' daily functioning, caregivers' sense of competence in interaction with the patient, on quality of life and mood of both and on costs of dementia care [25-28].

This article presents the design of the WHEDA study evaluating, whether (1) the positive results are replicable in a German multi-centre context and (2) the results remain stable in a prolonged follow up period. The methods are reported according to the requirements and structure of the CONSORT-statement including the extensions for non-pharmacological [29,30] and pragmatic trials [31].

## Methods

### Design

In this pragmatic non-pharmacological intervention trial, a randomised controlled design is being used in seven health care centres and has the following research aims:

#### Primary outcome

To compare the effects of a community occupational therapy programme (COTP) with a community occupational therapy consultation (COTC) on daily functioning of older people with dementia.

#### Secondary outcomes

• To evaluate the effectiveness of the COTP on patients' and caregivers' quality of life, mood and satisfaction with treatment and on caregivers' sense of competence and hours of care compared to those having a COTC.

• To evaluate the cost of both interventions from a societal perspective.

The intervention group receives ten sessions of occupational therapy during five weeks of one hour duration. The control group receives one home consultation of one hour duration by an occupational therapist within the same period. Measurements for both groups are at baseline before intervention (week 0), after intervention (week 6) and at follow-up (week 16, 26 and 52). Measurements of cognitive decline are applied one week before baseline and at week 11 and week 21 after baseline.

